
#### Secondary, user-centred outcomes.

For the assessment of child’s sleep quality, we used the Children’s Sleep Habits Questionnaire (CSHQ, 14]). The CSHQ is a retrospective screening instrument designed to examine children’s sleep [14]. It consists of 48 items, with 33 items distributed among various subscales, including bedtime problems, difficulties in falling asleep, sleep duration, anxiety, nighttime awakenings, parasomnias, breathing disorders, and daytime sleepiness. These subscales are utilized to calculate an overall score, providing a comprehensive evaluation of children’s sleep. Additionally, bedtime, the child’s average amount of sleep per day, duration of nocturnal wakefulness, and morning awakening time are recorded [14]. The German adaptation of Schlarb [15] is used, which was validated and normed by Schlarb, Schwerdtle, and Hautzinger [16] among a German norm sample consisting of 298 parents of 4–10-year-old children and 45 parents of children with sleep disorders.

To cover more aspects of sleep quality, we amended the CSHQ [14–16] by the Sleep inventory for children (Schlafinventar für Kinder und Jugendliche, SI-KJ; [17]). The retrospective, 33-item screening instrument supplements the survey by assessing sleep hygiene and sleep environment characteristics as well as physical factors contributing to sleep problems [17]. The questionnaire contains the main scale sleep and daily behaviour and the subscales sleep onset and sleep through problems, vegetative symptoms, daytime sensitivity, and nocturnal events. Data on various characteristics of sleep hygiene and sleep environment as well as physical factors, e.g., health problems such as allergies or chronic diseases are assessed. The instrument has been validated and normed on a German norm sample of 5–11-year-old children and parents [17].

We used the German version of the KiddyKINDL and KidKINDL, retrospective 24-item instruments to assess the health-related quality of life [18,19]. The KiddyKINDL is administered to guardians of 6-year-old children, and the KidKINDL is administered to guardians of 7–12-year-old children. Contents of the questionnaires are the subscales physical well-being, psychological well-being, self-esteem, family, friends, and functioning in daily life (school or preschool/kindergarten), with 4 items each [18,19]. Both versions are publicly available, have been psychometrically tested [20] and German normative scores are available [21].

To assess parenting stress, we used the German version of Abidin’s Parenting Stress Index (Eltern-Belastungs-Inventar, EBI; [22,23]). According to the retrospective 48-item instrument, parenting stress occurs when there is a mismatch between the demands of the parenting role and the coping resources needed to meet them. The demands arise from different sources of stress (child-related, parent-related and context-related), which are assigned to the child domain and the parent domain within the questionnaire. The child domain includes 5 subscales to assess the characteristics and behaviors of the child that result in demands on the parents, with 4 items for each subscale. This includes specific behavioral dispositions of the child (distractibility/hyperactivity, adaptability, demandingness, and mood), as well as interactions between child and parental characteristics (parental acceptance). The parenting domain includes 7 subscales to assess limitations in parental functioning that affect the resources available to cope with the demands of parenting and caring for children, with 4 items per subscale. This includes specific behavioral dispositions of the parents (depression, parental competence and parental attachment), as well as their available resources (social isolation, partner relationship, health and personal limitations). The instrument has been validated on German samples of 0.5-21-year-old children and their parents and German normative scores for mothers aged between 20 and 53 years are available [23]. For this study, parenting stress will be explored using the total score. In an exploratory manner, the 5 subscales of the child domain and the 7 parental domains will be analysed separately as well.

### Sociodemographic variables and covariates

At T0, sociodemographic characteristics and relevant covariates that have been identified in advance through a literature review are collected, including household size (“How many people live in your household all the time, including yourself?”, “Do other children live in your household besides the child with whom you are participating in our study?”; [24]), parental education (“What is your highest educational achievement?”; [24]), parental income (“Approximately what is the total average monthly net income of your household?”; [25]), relationship conflict between parents and parental separation (“Which marital status describes you best?”, “How would you describe your satisfaction with your relationship?”; [26,27]), sleeping together in the same bed (assessed through the SI-KJ; [28], child media use before bedtime (“How often does your child use electronic media before sleeping?”, “What electronic media does your child use before sleeping?”; [29]), and presence of media in the child’s sleep environment (“Is there electronic media in your child’s room?”, “What electronic media is in your child’s room?”; [30]). Covariates are assessed by categorial variables.

### Sample size

With regard to the required sample size, two factors were considered in the present study: The Aumio app for the children and the parent training. For the parent training, we first considered effects on child outcomes as a basis for sample size calculation. An average effect size of parent training of d = 0.20 was found in a meta-analysis on the effectiveness of family-based prevention interventions [31]. An average effect size of d = 0.21 of universal prevention programs was found in a meta-analysis on German-language effectiveness research [32]. Based on these findings, with an assumed power of.90, an alpha error level of.05, and an effect size of.21, a required sample size of 196 was calculated using the software g*Power [33].

Considering the drop-out rate (DOR) observed in the unpublished master’s theses on the Aumio app, this was also considered for sample calculation. In one of the most recent master’s theses on the effectiveness of the Aumio app, a drop out of 57.14% was found in the treatment group. Based on an expected DOR of 0.57, the number of cases is multiplied by the correction factor 1/(1-DOR) [34]. If the previously calculated sample size is increased by the expected DOR, a final required sample size of 456 is needed.

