### Statistical methods

#### Statistical methods for primary and secondary outcomes.

Descriptive methods including the calculation of appropriate summary measures of the empirical distribution (mean, standard deviation, median, minimum and maximum for continuous variables, and frequency in percentages for categorical variables) and specification of missing observations are used to present socio demographic data, feasibility, acceptability (with the Aumio app and the email course) and data on app use. In addition to the quantitative analysis of feasibility and acceptability, open-ended responses will be examined for recurring themes and categorized in a structured manner to provide additional context and insight into user experiences.

Preliminary intervention effects on the outcomes are analyzed by repeated measures ANOVA. Furthermore, the study will explore the relationship between the intensity of use and the outcomes. This analysis will involve both app usage as continuous measure, and categorization of the intensity of use into four levels (e.g., 12, 18, 24, and 30 uses during the intervention period). We will assess whether significant effects on the outcomes are observed at different levels of app use. All statistical analyses will be performed using R.

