Lastly regarding the analysis of the preliminary efficacy, the study design of the present research project, the single-group pre-post design, must be considered critically in itself. The methodological weaknesses were summarised by Maier-Riehle and Zwingmann [39]. First, the effect sizes cannot be interpreted causally because the observed changes are not exclusively attributed to the intervention but also to other confounding causes. In addition, different calculation methods are proposed for determining effect sizes in the single-group pre-post design. As a result, effect sizes are not comparable among each other and lead to different patterns of results. Last, it should be noted that Cohen’s limits of interpretation cannot be invoked when interpreting effect sizes, as these are based on independent samples and provide an overly optimistic measure in designs without a control group. No alternative limit of interpretation for effect sizes in single-group pre-post designs has been established at this time [39]. Nevertheless, the inclusion of covariates which possibly influence the primary and secondary outcomes aims to provide a more detailed picture of the preliminary efficacy of the Aumio app and can further prepare a larger, RCT with the focus on testing the efficacy of the Aumio app.

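### The stated 90% power matches a one-sided paired t-test that the plan never names; for the planned repeated measures ANOVA the same inputs give about 75–87%

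*Protocol article*

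**What the plan says.** The Sample size section takes its effect size from published meta-analyses: "An average effect size of d = 0.21 of universal prevention programs was found in a meta-analysis on German-language effectiveness research". It then gives the design values and the result, computed in g*Power: "with an assumed power of.90, an alpha error level of.05, and an effect size of.21, a required sample size of 196 was calculated". For dropout it says "Based on an expected DOR of 0.57, the number of cases is multiplied by the correction factor 1/(1-DOR"), and concludes that "a final required sample size of 456 is needed".

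The section does not say which test was entered into the software, whether alpha is one- or two-sided, how many measurements were assumed, whether 0.21 is standardised on the raw SD or on the SD of the change, or what pre-post correlation applies.

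The statistical methods for primary and secondary outcomes say: "Preliminary intervention effects on the outcomes are analyzed by repeated measures ANOVA". The trial design section sets three assessments: T0, T1 at six weeks and T2 at twelve weeks. The Objectives word the efficacy hypotheses directionally (better sleep quality, higher quality of life, lower parenting stress), but no section declares one-sided testing.

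**The concern.** A power figure belongs to a particular test. If 196 was obtained for a one-sided paired comparison, the 90% does not carry over to a non-directional ANOVA over three time points. The scale of the effect matters too. A d of 0.21 from prevention-programme meta-analyses equals a dz of 0.21 only when the pre-post correlation is .5, and no correlation is given.

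This calculation is the only stated basis for enrolling 456 dyads. If the 90% is taken at face value, a non-significant efficacy result could be read as stronger evidence against a change of 0.21 than the planned analysis provides. The Discussion says the results will inform a future randomised trial.

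**Working it through.** **Inputs from the article:** power .90, alpha .05, effect size 0.21, n = 196, dropout 0.57, enrolled 456 (all Sample size); repeated measures ANOVA (Statistical methods); three time points (Trial design).

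**Assumptions made here, not in the article:** compound symmetry for the ANOVA; the shape of change over T0, T1 and T2; the pre-post correlation r, shown over a range.

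**1. Reproduce 196.** For a paired t-test the noncentrality is dz·√n with n − 1 degrees of freedom.
- One-sided, dz = 0.21: power is .8993 at n = 195 and .9006 at n = 196. The smallest n reaching .90 is 196, an exact match. At n = 196 the noncentrality is 0.21 × 14 = 2.94.
- Two-sided, dz = 0.21: power reaches .90 at n = 241.
- Two independent groups: 389 (one-sided) or 477 (two-sided) per arm, which fits neither the figure nor the one-group design.
- Repeated measures ANOVA, f = 0.21/2 = 0.105, three measurements, r = .5: 193. The MANOVA form of the same input gives 195.

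The last two come close but do not return 196. Their input is also inconsistent with d = 0.21: over three time points, means spanning 0.21 SD give f of at most √(0.0294/3) = 0.099.

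**2. Reproduce 456.** 196/(1 − 0.57) = 196/0.43 = 455.8, rounded up to 456. The dropout step is correct.

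**3. Two-sided T0–T2 comparison at n = 196, dz = 0.21.** Power is .833. Power of .90 needs 241 completers (241/0.43 = 560.5, so 561 enrolled), or dz = 0.233 with 196 completers.

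**4. Three-time-point F at n = 196, r = .5.** The noncentrality is λ = n·Σ(μⱼ − μ̄)²/(1 − r), with 2 and 390 degrees of freedom. Means are in raw-SD units; at r = .5 a T0–T2 change of 0.21 SD is also dz = 0.21.
- Linear change, means 0, 0.105, 0.21: Σ = 0.02205, λ = 196 × 0.02205/0.5 = 8.64, power .749. Power of .90 needs 289 completers.
- Full change by T1, means 0, 0.21, 0.21: Σ = 0.0294, λ = 196 × 0.0294/0.5 = 11.52, power .867. Power of .90 needs 217 completers.

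**5. If 0.21 is a raw-SD effect.** Then dz = 0.21/√(2(1 − r)). With 196 completers:

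| r | dz | Two-sided T0–T2 power | Three-time-point F (linear to full change by T1) |
|---|---|---|---|
| .3 | 0.177 | .70 | .59–.73 |
| .5 | 0.210 | .83 | .75–.87 |
| .6 | 0.235 | .905 | .84–.93 |
| .7 | 0.271 | .965 | .93–.98 |

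**The case against.** - **The test is inferred.** The article names the software but not the test, it condenses a fuller plan that is not shown, and other routes land within three of 196. This stands: the supportable statement is that 196 matches a one-sided paired t-test. A reader might go further and say the figure is known to come from that test; the article does not show this.
- **The shortfall is conditional.** If 0.21 is a raw-SD effect and r is about .6 or higher, the two-sided comparison reaches 90%; at r = .7 the three-time-point F does so under both patterns of change. A reader might therefore conclude that the stated power is simply wrong. The documents do not support that without conditions. Equally, they state no correlation, so the 90% cannot be shown to rest on one.
- **The hypotheses are directional.** A one-sided T0–T2 contrast would have the stated power. This is a legitimate way to reconcile the text, but it has to be declared, and an ANOVA F-test is not that contrast.
- **Two further inferences do not hold.** The Discussion's caution that Cohen's limits "cannot be invoked when interpreting effect sizes, as these are based on independent samples" concerns how results are labelled, not planning inputs, so it does not show that 0.21 is on the wrong scale. Nor does the article say that the omnibus F decides the hypotheses; contrasts are a detail it may leave to a fuller plan.
- **The stakes are limited.** The primary feasibility and acceptability outcomes are analysed descriptively, and the Discussion already denies a causal reading of the effect sizes. This stands, and it lowers the severity.

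**Conclusion.** The concern holds as a mismatch between the sample size statement and the planned analysis. The size of the gap depends on two things the article leaves open: the scale of the effect and the pre-post correlation. With 0.21 as dz, or as a raw-SD effect at r = .5, the chance of missing the effect is about 17% for a two-sided T0–T2 comparison and 13–25% for the three-time-point F, against the 10% implied. The F-test figures also assume compound symmetry and a pattern between linear change and full change by T1.

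Severity is moderate. The sample size justification needs correcting; the primary analysis is unaffected and the enrolment target need not change.

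**What to change.** Keep 456 and restate what it provides for the analysis to be run. Suggested wording:

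> 196 completers give about 83% power (two-sided alpha .05) for a T0–T2 within-person change of dz = 0.21, and 90% for dz = 0.23.

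Add whether 0.21 is standardised on the raw SD or on the SD of the change, and the pre-post correlation assumed. A short table over r, as above, would cover the uncertainty.

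Alternatively, if one-sided testing was intended, name the one-sided paired test in the Sample size section and declare a one-sided T0–T2 contrast in the Statistical methods, so that the two agree.

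The cost is one paragraph and no extra participants. Under the first option the quoted power becomes less favourable; under the second the trial commits to a one-sided test.

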### Recruitment and treatment allocation

Participants are recruited and allocated consecutively. Study participants are mainly recruited through the Aumio app. After downloading the app in the app store, five percent of new users are offered the chance to enrol in the study before they start using the app for the first time. Recruitment will be augmented by advertisements in pediatric clinics and online, where a link to the website in the survey platform for informed consent is provided. If parents are interested in the study, they will be redirected to a dedicated page within the app. On this page, both children and guardians receive information about the opportunity to participate in the study. Participants are informed about the purpose and process of the survey, as well as possible advantages and disadvantages of participating. They will be informed that participation in the study is completely voluntary and that participation can be terminated at any time without giving reasons. Furthermore, participants will be informed about their rights regarding data storage, data protection and data deletion. Informed consent will be obtained from both guardians and children in child-friendly language.

### Plans to promote participant retention and complete follow-up

In return for participating, participants will receive free access to the entire Aumio app for one year. They also receive a 30 euro shopping voucher for completing the last survey (T2).

### Relevant concomitant care permitted or prohibited during the trial and Provisions for post-trial care

Participation in the current study does not affect any potential concomitant treatment during the study period. All participants will receive contact information of the study team and will be able to access evidence-based informational materials on infant sleep through the Aumio website at any time.

### Data collection and management

#### Plans for assessment and collection of outcomes.

The collection of the questionnaire data will be done using the German server of Tivian GmbH (UniPark), which specialises in the secure collection of data in the field of research and is certified with ISO 27001 by the German Federal Office for Information Security.

#### Data management.

The data of the questionnaires and the data of the app are collected separately, and the assignment is only possible via an assignment list, which are exclusively encrypted and password-protected and stored locally in separate folders. The hard drive will be located at Freie Universität Berlin.

No sensitive, personal data is collected via the Aumio app, but only data that has a technical background (e.g., device identification and information, language, etc.) and represents user behaviour (e.g., number and duration of app use). Furthermore, the data is only collected under a pseudonym, which is created by the participants themselves at T0. The pseudonym consists of the first two letters of the participant’s first name, the last two digits of their current ZIP code, and the first two letters of the name of the participant’s first child.

#### Confidentiality.

The data is only accessible to the study team. In addition, the data from Unipark and the data from the survey are assigned via an assignment list. This is password-protected, encrypted and only accessible to the study team. The data obtained are merged and then analysed completely anonymously. It is not possible to draw conclusions about individual persons. The data are only evaluated as a whole. All data are only stored locally or on a hard disk (as a back-up) in a password-protected manner. The required password is only accessible to the study team. The study team agrees to maintain confidentiality about personal data and to comply with the Federal Data Protection Act. No personal data will be passed on to third parties or published.

### Statistical methods

#### Statistical methods for primary and secondary outcomes.

Descriptive methods including the calculation of appropriate summary measures of the empirical distribution (mean, standard deviation, median, minimum and maximum for continuous variables, and frequency in percentages for categorical variables) and specification of missing observations are used to present socio demographic data, feasibility, acceptability (with the Aumio app and the email course) and data on app use. In addition to the quantitative analysis of feasibility and acceptability, open-ended responses will be examined for recurring themes and categorized in a structured manner to provide additional context and insight into user experiences.

Preliminary intervention effects on the outcomes are analyzed by repeated measures ANOVA. Furthermore, the study will explore the relationship between the intensity of use and the outcomes. This analysis will involve both app usage as continuous measure, and categorization of the intensity of use into four levels (e.g., 12, 18, 24, and 30 uses during the intervention period). We will assess whether significant effects on the outcomes are observed at different levels of app use. All statistical analyses will be performed using R.

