### Objectives

The aim of this pilot study is to test the feasibility, acceptability and preliminary efficacy of the Aumio app and the parent-centred email psychoeducation module. We aimed (1) to examine the feasibility and acceptability of the of the Aumio app and the parent-centred email psychoeducation module. We therefore aimed to conduct qualitative and quantitative data to gain comprehensive insights. In addition, we also aimed (2) to collect information for improvements of the Aumio app and the parent-centred email psychoeducation module from a user’s perspective. We furthermore aimed (3) to examine the preliminary efficacy of the Aumio app and the parent-centred email psychoeducation module. As secondary user-centred outcomes, we aimed to examine whether its use improves children’s sleep, covering a broad range of facets to adequately capture the multidimensional nature of sleep. Furthermore, preliminary efficacy on child’s health-related quality of life and effects on parental stress will be tested as secondary user-centred outcomes. In order to further improve the feasibility and to synthesize recommendations for use, it will be investigated (4) at which intensity of usage the Aumio app significantly affects the feasibility and satisfaction as well as the secondary user-centred outcomes. The intensity of usage will be analysed continuously as well as divided into 4 levels (12, 18, 24, and 30 uses during the study period) and included in the analyses.

The primary, feasibility hypothesis refers to the user’s subjective perspective on the Aumio app and the parent-centred email psychoeducation module, with the assessment time points 6 weeks after the start of the app use, at the midpoint of the 12-week parent-centred email psychoeducation module and again another 6 weeks after. We hypothesize that the Aumio app and the parent-centred email psychoeducation module is feasible. We also hypothesize Aumio app and the parent-centred email psychoeducation module is accepted among the users. We further hypothesize that the present study design is feasible to conduct a large scale trial on the effectiveness.

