The secondary, user-centred hypothesis refer to comparisons of endpoint scores pre app use, at the same time points as the feasibility survey. We hypothesize that 6 weeks and 12 weeks after the start of the app use, children’s sleep quality will be significantly increased (secondary, child-centred endpoint) and health-related quality of life will be significantly higher (secondary, child-centred endpoint). Furthermore, we hypothesize that parenting stress will be significantly reduced 12 weeks after the start of the use of the email psychoeducational program (secondary, parent-centred endpoint). Exploratory analyses will also be conducted to determine to what extent usage behavior influences the effects on primary and secondary outcomes.

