### Trial design and study setting and participant timeline

The present research project is designed as a one-group pre-post pilot study. As this trial is the first larger scale pilot trial on the feasibility and acceptability as well as the first trial on the preliminary efficacy of the app on sleep quality and the parent module, randomization, control groups, and blinding do not apply to the study design of this trial. The study is a single study conducted in the naturalistic setting of the app, meaning it was conducted exclusively in-app and within a German-speaking population. After consenting to participate in this study, the participants will be provided a 12-months free access to the Aumio app and receive the parent-centred email psychoeducation module at weekly intervals.

Once participants agree to the conditions of participation and meet the inclusion criteria, guardians are directed to the first assessment (T0). At T0, at the beginning of the intervention and before the first app use, data on sociodemographic characteristics and relevant covariates and the outcomes will be collected. After completing the first survey T0, participants are provided with free access to the Aumio app for one year and receive the parent-centred email psychoeducation module once a week. The intervention duration is set at twelve weeks. Six weeks after the intervention start and the first app use, the second measurement point (T1) takes place, where primary and secondary outcomes are assessed. Immediately following the conclusion of the 12-week intervention, the third measurement point (T2) is conducted, comparable to the T1 assessment (Fig 1).

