### Outcomes

#### Primary, feasibility outcome.

Feasibility will be assessed by the number of users, dropout rates, and usage patterns (e.g., number of audio content played). Usage behavior of the parent-centred email psychoeducation module will be assessed weekly using a content related quiz question in the Aumio app. The recruitment process will further be examined by analysing the study outreach method and its consequences on participant recruitment.

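### App use counted over all 12 weeks is related to outcomes that include week 6, so use after T1 can enter the explanation of T1 scores, and part of feasibility is regressed on itself

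*Protocol article*

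**What the plan says.** **Exposure.** The Objectives say that intensity of use will be analysed continuously and also "divided into 4 levels (12, 18, 24, and 30 uses during the study period". The statistical methods repeat the levels, as examples: "categorization of the intensity of use into four levels (e.g., 12, 18, 24, and 30 uses during the intervention period". The trial design section fixes the period: "The intervention duration is set at twelve weeks". No other usage window is given, and none at all for the continuous measure.

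**Outcomes.** At week 6 "the second measurement point (T1) takes place, where primary and secondary outcomes are assessed". The last assessment follows at week 12: "Immediately following the conclusion of the 12-week intervention, the third measurement point (T2) is conducted". Week 6 is a hypothesis time point in its own right: "We hypothesize that 6 weeks and 12 weeks after the start of the app use, children’s sleep quality will be significantly increased".

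**The link.** The statistical methods relate intensity of use to the outcomes with no limit by type or time point. The Objectives put it this way: "Exploratory analyses will also be conducted to determine to what extent usage behavior influences the effects on primary and secondary outcomes". They also name feasibility and satisfaction among the things that intensity of use may affect, and give recommendations for use as the purpose.

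**Feasibility.** The outcome section defines it: "Feasibility will be assessed by the number of users, dropout rates, and usage patterns (e.g., number of audio content played". It adds use of the email module, measured by a weekly quiz question, and the recruitment process.

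**The concern.** An explanatory variable should be complete before the outcome that it explains. A 12-week count is not complete at week 6, and use is self-selected: families are encouraged to fit the app into their routine as suits them, and no reminders are sent. A family's experience by T1 can therefore change how much it uses the app afterwards. That later use goes into the same total, so the result at T1 helps to produce the exposure said to explain it.

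The second problem is simpler. If feasibility is measured by how much the app is used and by who drops out, asking how usage affects feasibility partly asks how usage affects usage.

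At stake are the recommendations for use. The plan looks for the level of use at which effects become significant. A level found this way at T1 could reflect who carried on after week 6, and a real relation could be hidden if satisfied families stopped.

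**Working it through.** **1. The windows side by side**

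| Quantity | Window or time | Section of the protocol article |
|---|---|---|
| Uses, levels 12/18/24/30 | whole 12-week period | Objectives; Statistical methods |
| T1 outcomes | week 6 | Trial design |
| T2 outcomes | end of week 12 | Trial design |

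For T2 the exposure window ends when the outcome is measured. For T1 half of the window, 6 of 12 weeks, lies after the outcome.

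**2. What a level says about exposure before T1**

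At an even pace, weekly use is level/12 and use by T1 is level/2:

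| Level | Per week | By T1 |
|---|---|---|
| 12 | 1.0 | 6 |
| 18 | 1.5 | 9 |
| 24 | 2.0 | 12 |
| 30 | 2.5 | 15 |

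At an uneven pace, a family with 24 uses in total may have had anything from 0 to 24 of them by T1. The level does not fix exposure before T1.

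**3. Sample size for the illustration**

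The Sample size section gives d = 0.21, power 0.90, alpha 0.05 and n = 196. A one-sided paired t test reproduces 196. The inflation also reproduces: 196/(1 - 0.57) = 455.8, rounded up to 456. These figures are not in dispute; 196 is the number the plan expects to complete.

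**4. Size of the bias at T1**

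The documents give no feedback strength, so this is an illustration on stated assumptions, with 3,000 simulated trials per row:

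- Family tendency a ~ Normal(0, 0.5).
- Uses in weeks 0-6 ~ Poisson(12 x exp(a - 0.125)), mean 12.
- T1 change y ~ Normal(0, 1), independent of use, so there is no true effect.
- Uses in weeks 7-12 ~ Poisson(12 x exp(a - 0.125 + g x y - g²/2)).
- Test: Pearson correlation of use with y, p < 0.05.

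Here g is the change in log-rate per SD of T1 change. Since exp(0.1) = 1.11 and exp(0.3) = 1.35, g = 0.1 and g = 0.3 mean about 11% and 35% more later use for a family 1 SD better at T1.

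| g (n = 196) | 12-week use: significant | Mean r | T1 gap in SD, 24 or more uses vs fewer | Use up to T1: significant |
|---|---|---|---|---|
| -0.3 | 94.4% | -0.25 | -0.42 | 4.7% |
| -0.2 | 68.6% | -0.17 | -0.29 | 4.9% |
| -0.1 | 22.4% | -0.09 | -0.15 | 5.1% |
| 0 | 5.3% | 0.00 | 0.00 | 5.3% |
| 0.1 | 24.3% | 0.09 | 0.15 | 4.8% |
| 0.2 | 68.7% | 0.17 | 0.29 | 4.7% |
| 0.3 | 94.6% | 0.25 | 0.43 | 4.8% |

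At n = 456 the 12-week rates are about 46%, 96% and 100% at |g| = 0.1, 0.2 and 0.3. For scale, the plan's design effect is 0.21 SD.

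The last column stays near 5% because the model has no feedback before T1. It shows that the window mismatch is removed, not that every bias is.

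**5. Circularity**

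If each use is one audio play, uses and plays are the same count and correlate 1.0. If plays average 1.5 per use (assumed), the correlation is 0.99. Dropout is closely tied, since families who leave accumulate fewer uses. Satisfaction, quiz use and recruitment are measured separately.

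**The case against.** **The T1 pairing is inferred.** No sentence says that T1 scores will be related to 12-week use. The levels in the statistical methods are examples, and an analysis plan not shown may give windows. This stands as a limit on the claim: a reader might infer that the protocol expressly plans this pairing, and it does not. But the only window stated is the full period, the outcomes are unrestricted, and T1 is a hypothesis time point, so an analyst who follows the text can do exactly this.

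**The direction is unknown.** It is tempting to say that improved families carry on and that the bias must favour the app. Nothing in the protocol supports that. Families whose child sleeps better may stop, and the table is symmetric.

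**The size is assumed.** This is correct. A single high figure would mislead; the range from about 5% to 95% is the honest statement.

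**The analysis is already hedged.** The Objectives call it exploratory, the abstract speaks of association, and the Discussion says that pre-post effect sizes cannot be read causally. That lowers the stakes. None of it addresses exposure counted after the outcome, and the analysis is still meant to yield recommendations for use.

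**Circularity is partial.** This also stands. It would be wrong to infer that the whole feasibility and acceptability outcome is circular.

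**Matching windows does not end feedback.** This is true. In one set of assumptions with no effect of use, where week-3 improvement raised use in weeks 4-6 (log-rate 0.3-0.5, correlation 0.5 between week-3 and T1 change), 28-47% of trials were significant even with use counted only up to T1. This limits what may be concluded from the repaired analysis; it is no reason to keep exposure that falls after the outcome.

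**Conclusion.** The concern holds in limited form. Read as written, the plan lets use in weeks 7-12 enter the explanatory variable for T1 scores. Any feedback from T1 status to later use then biases the T1 association, in a direction that cannot be known in advance. The false-positive rates and the spurious gaps of 0.15 to 0.43 SD rest wholly on the assumed feedback strength and spread of use; with no feedback the error rate stays at its nominal level.

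The mismatch does not touch T2, although self-selected use and feedback within the 12 weeks remain there. The circularity covers usage patterns by construction and dropout closely, and nothing else. This is worth correcting because the repair is inexpensive and the result feeds the recommendations for use; it does not undermine the study's descriptive feasibility aims.

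**What to change.** 1. Relate T1 scores, adjusted for T0, to uses up to T1, with the analysis levels scaled to six weeks (for example 6/9/12/15, half of 12/18/24/30).
2. Relate T2 scores, adjusted for T0, to uses up to T2, with the levels as they stand. State the same windows for the continuous measure.
3. If use in weeks 7-12 is examined separately, adjust that term for the T1 score and early use. Do not read the T1-adjusted coefficient of early use as its total effect, because adjustment removes whatever runs through T1. For example, if early use raises T1 by 0.30 per SD and acts on T2 only through T1, with a true total effect of 0.21, the adjusted coefficient is 0.00.
4. Remove usage- and dropout-based feasibility from the outcomes of the usage analysis and report them descriptively, as already planned. Keep satisfaction and the user-centred scores.
5. State that recommendations for use rest on associations, since self-selection and feedback within each window remain.

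**Cost.** Wording only, with no new assessments. A six-week count makes the T1 estimates somewhat less precise. App use must be separable by date; the Data management section mentions number and duration of use but does not say that dates are kept, so this should be confirmed.
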